### Allocation

Computer generated codes numbered 1–50 will be used to assign patients to either the intensive arm or the standard care arm. The randomization procedures are as follows:
The physician or nurse will explain to eligible patients about the international recommendation on performing regular follow-up to detect silent risk factors and complicationsThey will also explain to patients the need to assess the effectiveness of using a team to implement structured care by comparing the latter with usual careAfter the patient has signed the consent form, a study team member will open the envelope containing the randomization group and sign and date the envelopeThe signed envelope will be kept by the nurse in a secure place for audit purposesThe nurse will explain to the patient whether they have been randomized to the intensive arm or standard care arm and the assessment will proceed accordinglyThe nurse will keep a log of randomized patients and record status including study completion, premature discontinuation, withdrawal of consent or loss to follow-up

### Interventions

#### Intensive care group visits and counseling

##### Multi-disciplinary team trained in motivational interviewing techniques

Patients will be managed by a multi-disciplinary team consisting of an endocrinologist, a DNE, a renal pharmacist and an MSW. This shifts the traditional physician-centric management to structured physician, DNE, MSW and pharmacist clinic and telemedical follow-up. This multi-disciplinary team will aim to treat to treatment targets and provide comprehensive, structured, piece-meal, interactive-style counseling incorporating structured counseling on the essential self-care behavior in people with diabetes mellitus that predict good outcomes. All healthcare providers involved in this multi-disciplinary team will be trained in motivational interviewing techniques.

##### Endocrinologist clinic review

The endocrinologist clinic review will include review of blood and urine test results, weight and blood pressure. Medication will be adjusted to achieve HbA1c, low density lipoprotein-C (LDL-C) and blood pressure and urine ACR targets.

##### DNE clinic review and telephone reviews

The DNE will counsel the patient at recruitment and follow up the patient’s self-blood glucose monitoring (SBGM) readings and food diary via telephone calls and messages, and in suitable patients who prefer to use a smartphone application, via the “CGH Diabetes Diary” application. Additional face-to-face clinics sessions will be arranged according to clinical discretion. The DNE will prepare a clinic folder for each patient and create a system to facilitate appointment booking and tracking of default. Between each follow-up visit, the DNE will contact the patient by phone or email to remind them of the appointments (e.g. medical follow-up visit or laboratory tests), remind them to adhere to medications and healthy lifestyles, perform and report self- glucose monitoring, advise on insulin dose titration and provide psychosocial support, as appropriate. Before each follow-up visit, the nurse will ensure that results of all blood and urine tests ordered by the physician are available in the clinic review folder for decision making. At each follow-up visit, the patients will first see the nurse to record blood pressure, body weight and urine and blood tests in the clinic review folder. The patient’s compliance will also be checked at each visit. The patients will see the nurse after the folow-up visit, to clarify any issues and concerns. The nurse will reinforce compliance and record any changes in medications, and note any procedures or tests ordered by the doctor. After each follow-up visit, the nurse will issue summary reports to be given to patients and physicians to promote sharing of information.

##### Renal pharmacists

Renal pharmacists will be involved in the care of the patient if blood pressure measured during the endocrinologist consultation is not at target and requires more intensive medication titration. The first appointment with the pharmacist will be scheduled 2–4 weeks after the endocrinologist’s referral, during which there will be a review of the patient’s compliance to antihypertensive agents, any side effects, renal panel results if an angiotension converting enzyme (ACE)-inhibitor or angiotensin-receptor blocker (ARB) was started or increased in dose, and home blood pressure measurements. The pharmacist will measure and document the blood pressure and heart rate in clinic and adjust the dose of antihypertensive agent(s) to meet the blood pressure goal according to the hospital’s hypertension guideline. The pharmacist will also counsel and educate the patient on blood pressure management and drug therapy where appropriate. The next appointment with the patient and any necessary blood test will then be arranged; intervals between each appointment may range between 2 weeks and 3 months during the period of dose titration. Once target blood pressure has been reached and blood pressure is stable, no further follow-up with the pharmacist will be scheduled unless requested by the endocrinologist.

##### Dietitian

The dietitian will counsel the patient at recruitment and further follow-up clinic sessions will be arranged according to clinical need and discretion. Patients will be counseled on eating behavior in line with American Diabetes Association nutrition therapy recommendations for the management of adults with diabetes mellitus [14].

##### Medical social worker

The MSW will hold six follow-up sessions (three face-to-face and three telephone follow-ups), at 3-weekly intervals, with intervals for follow-up varying according to the participant’s readiness and motivation. The first session will include administration of the Diabetes Distress Scale-17 (DDS17) [15], Medication Adherence Report Scale-5 (MARS-5) [16] assessment of the patient’s knowledge of his/her condition, his/her awareness and motivation level, engagement of the caregiver (if applicable) and goal setting. The six sessions will focus on using health change methodology to discuss seven essential self-care behaviors that predict good outcome in diabetes mellitus: healthy eating, being physically active, monitoring of blood glucose, compliance with medications, good problem-solving skills, healthy coping skills and risk-reduction behavior.

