#### Other endpoints

Other endpoints include (1) change in the MARS-5 for compliance and (2) change in the DDS17 scores.

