### Data collection methods

Patients will be weighed (wearing light clothing without shoes) using a calibrated electronic scale and recorded to the nearest 0.01 kg and height will be measured with a portable stadiometer to the nearest 0.1 cm (barefoot). Body fat percentage will be measured by bioimpedance electrical analysis using the Tanita TBF-300 Goal Setter body composition analyzer. Waist circumference will be measured by a non-stretch tape at the level midway between the lowest rib margin and the iliac crest and recorded to the nearest 0.1 cm, while the patient is standing. Hip circumference will be measured at the widest circumference at the level of the symphysis pubis and gluteus maximus.

Systolic and diastolic blood pressure (BP) will be measured at the left arm with patients seated and rested, with an appropriately sized cuff placed at the level of the heart using an automated sphygmomanometer.

Venous blood and urine samples will be collected after 10 h of fasting at week 0 and thereafter before every clinic review by the endocrinologist. These include samples for testing HbA1c, renal panel, calculated eGFR, fasting lipid profile (total cholesterol, triglyceride, LDL-C, HDL-C) and urine albumin:creatinine ratio.

Baseline, 4-month (after MSW intervention) and end-of-study MARS-5 and DDS17 questionnaires will be performed in both the intervention and control groups. The MARS-5 by Horne et al. has been widely used to assess patient adherence to medication in clinical research and medical practice. The DDS17 is a 17-item scale that captures four critical dimensions of distress: emotional burden, regimen distress, interpersonal distress and physician distress.

Philips Medical systems QLAB Quantification software for IMT will be used as the primary measurement tool for bilateral common femoral arteries (CFA) and superficial femoral arteries (SFA) [12, 17]. When automated measurements are not possible due to the course of the arteries or state of disease, manual measurements will be taken at the same specified anatomical landmarks.

The IMT is defined as the distance between two echogenic lines represented by the lumen-intima interface and media-adventitia interface of the arterial wall (Table 1).

**Table 1 Tab1:** Measurement details of femoral vascular imaging and IMT measurement. CFA, common femoral arteries; SFA, superficial femoral arteries

Assessment modality	B-mode ultrasonography	

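### The baseline for the DDS17 and MARS-5 change scores is probably taken after the arm is disclosed and, in the intensive arm, likely inside the first counselling session, leaving the between-arm difference in change open to bias

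*Protocol article*

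**What the plan says.** All references are to the protocol article.

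- **Order of steps (Allocation).** The patient signs consent, a study team member opens the envelope, and the nurse tells the patient the arm. Only then does assessment proceed. This applies to both arms.
- **First social-worker session (Medical social worker, intensive arm).** "The first session will include administration of the Diabetes Distress Scale-17 (DDS17", together with MARS-5, a review of knowledge and motivation, "engagement of the caregiver (if applicable) and goal setting". The order of these items within the session is not given. On the schedule: "The MSW will hold six follow-up sessions (three face-to-face and three telephone follow-ups), at 3-weekly intervals", and these intervals may vary by participant.
- **Other intensive-arm contacts at entry.** "The DNE will counsel the patient at recruitment" and "The dietitian will counsel the patient at recruitment". Neither section says whether this comes before or after the first social-worker session.
- **Standard care group visits and counseling.** Specialist visits, nurse and dietitian counselling and educational material are listed. A social worker is not.
- **Measurement times (Data collection methods).** "Baseline, 4-month (after MSW intervention) and end-of-study MARS-5 and DDS17 questionnaires will be performed in both the intervention and control groups". The person administering them, the setting and the order relative to allocation are not stated.
- **Standing of the scales (Other endpoints).** The endpoints are "change in the MARS-5 for compliance and (2) change in the DDS17 scores".
- **Analysis (Statistical methods).** Change in each scale is analysed by linear regression. The baseline score is not named as a covariate.
- **Blinding (masking).** Only the statistician is blinded.

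**The concern.** Both scales are self-reports, one of distress and one of adherence. Answers to such scales can depend on what the patient expects and on who is asking. A patient who has just learned that they will receive intensive support, or usual care, may answer differently from one who does not yet know. A patient reporting adherence to the professional who will counsel them on taking their medication may also answer differently from one who fills in a form elsewhere.

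The endpoints are changes from baseline. If the baseline is measured after allocation is known and under different conditions by arm, any resulting shift becomes part of the between-arm difference in change. Randomisation gives no protection, because the shift arises after it. At stake is the reading of two patient-reported endpoints, not the renal and cardiovascular primary endpoints or the secondary endpoints.

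**Working it through.** **Step 1. Is the first social-worker session the intensive-arm baseline?** Six sessions at 3-week spacing contain five intervals, so session 6 falls 5 × 3 = 15 weeks (about 3.5 months) after session 1. That fits the 4-month questionnaire, which Data collection methods places after the social-worker intervention. Session 1 is thus the natural matching 'before' measurement and the only administration described in detail. This makes the reading likely, but the text does not state it, and the schedule figure is not available here.

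**Step 2. What if it is not the baseline?** Then the intensive arm completes an additional round of both scales in a counselling session, for which the article describes no counterpart in standard care. The Allocation section still describes assessment as following disclosure. On either reading, the shown text does not place the baseline before the envelope is opened, and the conditions of measurement appear to differ by arm.

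**Step 3. How large could the effect be?** The article gives no figures for these scales, so this is illustrative.

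From the article: 25 per arm, two-sided 5% significance.

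Assumed: a differential baseline shift d of 0.2 or 0.3 SD, a correlation r of 0.5 between baseline and follow-up, equal SD at both visits, no shift at follow-up, no true treatment effect, normal approximation.

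*Unadjusted change score.* The size of the bias is d.
- SE = √(2(1 − r)) × √(2/25) = 1 × 0.283 = 0.283 SD.
- d = 0.2: d/SE = 0.707. P(|Z| > 1.96) = 0.105 + 0.004 = 0.109.
- d = 0.3: d/SE = 1.061. P(|Z| > 1.96) = 0.184 + 0.001 = 0.185.

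*With adjustment for the baseline score.* The size of the bias is r × d.
- SE = √(1 − r²) × √(2/25) = 0.866 × 0.283 = 0.245 SD.
- d = 0.2: bias 0.10, ratio 0.408. Error rate 0.060 + 0.009 = 0.069.
- d = 0.3: bias 0.15, ratio 0.612. Error rate 0.089 + 0.005 = 0.094.

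*Range over the assumed correlation, same formulas:*

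| r | d | SE unadjusted | Error rate unadjusted | SE adjusted | Error rate adjusted |
|---|---|---|---|---|---|
| 0.4 | 0.2 | 0.310 | 9.9% | 0.259 | 6.1% |
| 0.4 | 0.3 | 0.310 | 16.2% | 0.259 | 7.5% |
| 0.5 | 0.2 | 0.283 | 10.9% | 0.245 | 6.9% |
| 0.5 | 0.3 | 0.283 | 18.5% | 0.245 | 9.4% |
| 0.8 | 0.2 | 0.179 | 20.1% | 0.170 | 15.6% |
| 0.8 | 0.3 | 0.179 | 38.9% | 0.170 | 29.3% |

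Nearly all the extra rejections lie in one tail. Which arm they favour depends on the sign of the shift, and the documents do not settle that. Baseline adjustment reduces the bias but does not remove it.

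**The case against.** A reader might infer that the baseline is contaminated, and in the intensive arm only. The documents do not support that, for three reasons.

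- No section says that the session-1 questionnaires are the baseline. They could be a clinical tool to guide counselling, with a separate research baseline taken under Data collection methods. The schedule figure, which covers both scales, might settle this but is not available here, and that gap is no fault of the plan.
- The arm is disclosed to both groups, so knowledge of allocation is not specific to the intensive arm. Only the social-worker setting, and possibly prior nurse or dietitian counselling, is. Disclosure to both arms does not cancel the problem, though: learning of intensive care and learning of usual care can move answers differently.
- No shift has been shown. The scales may come first in session 1, before any counselling.

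The size is also open to challenge. The 0.2 to 0.3 SD shift has no source in the article. Patients stay unblinded, so if the same reporting tendency persisted at follow-up it would partly cancel in the change score. If patients report better adherence and less distress to the counsellor at baseline, the intensive arm would appear to improve less, and the bias would favour standard care. Calling this simply an inflated chance of a false benefit would be wrong.

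These points limit the claim to an exposure to bias of unknown size and direction. They do not remove it, because the sequence of consent, disclosure and assessment is written in the article, as is the use of the scales in a counselling session that standard care does not list.

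**Conclusion.** The point holds in limited form. The text as written probably places the DDS17 and MARS-5 baseline after disclosure of the arm in both groups and, in the intensive arm, likely with the person delivering the counselling. The between-arm difference in change is therefore open to bias that randomisation cannot remove.

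Under the stated assumptions (differential shift of 0.2 to 0.3 SD, r = 0.5, 25 per arm, no shift at follow-up), the two-sided error rate would be about 11 to 19% unadjusted and 7 to 9% with baseline adjustment. These figures show scale only; they do not estimate what will happen in this trial.

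The importance is low: both scales are other endpoints, and nothing here touches the primary or secondary conclusions. It is still worth correcting because the correction is simple.

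**What to change.** Amend three sections of the protocol.

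- **Allocation:** add a step, after consent and before the envelope is opened, in which the patient completes DDS17 and MARS-5.
- **Medical social worker:** replace administration of the two scales in the first session with use of the already completed baseline form.
- **Data collection methods:** state that both questionnaires are self-completed in the same setting and manner in both arms at baseline, 4 months and end of study.

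This reorders existing steps and adds no new measurement. The cost is a slightly longer consent visit before allocation. The change need not extend to femoral IMT imaging: the argument concerns self-reported scales, and requiring an ultrasound examination before the envelope is opened could delay randomisation.

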##### Equipment, technology and educational material

Equipment will be provided to suitable patients when clinically indicated and these include blood pressure monitors, glucometers, glucose test strips, lancets and android tablets. Patients whose blood pressure readings are not at target at clinic appointments will be taught and encouraged to take measure their own blood pressure and provided with a blood pressure machine. Patients with HbA1c not at target or with significant risks of hypoglycemia will also be provided with a glucometer, glucose tests strips and lancets and taught how and when to perform SBGM, instructed how to use either a written or smartphone logbook, instructed to take photographs of their meals and how to communicate with DNEs via the smartphone application or via messaging systems. Patients will also be taught how to activate smartphone applications or pedometers to measure daily activity. These aim to improve and increase patient-generated health data, communication of capillary blood glucose readings between patient and healthcare professional, diet and exercise, and act as communications channels through which individualized feedback can be given to the patient to specifically target glycemic control, blood pressure and exercise targets. Patients will also be provided with handouts and with tablets containing organized educational material including easy-to-understand and relevant videos and educational material to facilitate diabetes self-care.

#### Standard care group visits and counseling

Patients randomized to the standard care group will receive usual care, which consists of:
Scheduled, regular, 4-monthly, specialist outpatient care visits for review of blood pressure, HbA1c and other investigations, and titration of medications as per standard of careCounseling with the DNE according to standard of care and usual follow-up via a phone call with the DNE initiated by the patientProvision of educational materials on diabetes mellitus as per standard of careCounseling with the dietitian according to standard of care, based on the American Diabetes Association nutrition therapy recommendations for the management of adults with diabetes mellitus [14]

### Outcomes

The following endpoints will be evaluated.

#### Primary endpoints

The primary outcome measures are (1) rate of deterioration of chronic kidney disease (rate of decline of eGFR or worsening of proteinuria) or development of end-stage renal disease, whichever events happen and (2) cardiovascular events (composite events of acute myocardial infarction, revascularization procedures, heart failure, unstable angina, arrhythmia, stroke, transient ischemic attacks requiring hospital admissions) and related death, whichever events happen.

#### Secondary endpoints

Secondary outcomes include (1) proportion of patients with documented improved control of risk factors and fulfilment of two or more of the “ABC” targets as defined by (a) HbA1c < 7%, (b) blood pressure < 140/90 mmHg and (c) LDL-C < 2.6 mmol/L and/or two of the following changes in risk factor control: (d) at least 0.5% reduction in HbA1c, (e) at least 5 mmHg reduction in systolic BP, (f) at least 0.5 mmol/L reduction in LDL-C, (g) at least 3% reduction in body weight, (2) frequency of hypoglycaemia (in the last 3 months) (3) number of hospitalization days and (4) changes in femoral IMT.

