**Methods:**

The study is a single-center randomized controlled trial (RCT) with two study arms - intensive diabetes mellitus care versus routine clinical care. Patients in the intensive arm will receive care from a multidisciplinary team consisting of an endocrinologist, diabetes nurse educator, dietitian, renal pharmacist and medical social worker for counselling. In addition, patients will be provided with tools for self-care empowerment such as glucometers, blood pressure monitors and android tablets to facilitate care, monitoring and education. Patients in the routine clinical care arm will receive standard clinical care. Follow up (FU) will be for 3 years. Primary outcomes include cardiovascular events, rate of progression of nephropathy and development of end-stage renal disease. Secondary endpoints include the proportions of patients with documented improved control of cardiovascular risk factors (HbA1c, blood pressure, low density lipoprotein-C (LDL-C), reduction in body weight), frequency of hypoglycemia, hospitalization days and changes in femoral IMT. We will also examine the prevalence of peripheral atherosclerosis and the predictive value and usability of lower extremity arterial ultrasound to predict cardio-cerebrovascular events, amputation and peripheral intervention.

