### Eligibility criteria

Patients will be considered eligible for the study if they fulfil the following criteria:
Aged 21–70 yearsPoorly controlled T2DM as defined by HbA1c ≥ 9%Nephropathy as defined by estimated GFR (eGFR) 30–60 ml/min and/or proteinuria classified as urine protein > 0.5 g/day and/or urine albumin:creatinine ratio (ACR) >30 mg/mmol on two consecutive measurements 3 months apart

Patients will be excluded from study participation if any of the following criteria are present:
Type 1 diabetes mellitus defined as a history of ketosis at diagnosis (acute symptoms with heavy ketonuria (urine value > 3+) or ketoacidosis) or continuous requirement of insulin within 1 year of diagnosis.Psychiatric conditions being treated by medications that adversely affect patients’ weight and stability of their mental health.Patients on weight loss medications or have had bariatric surgery, which may affect their mental health and compliance with dietary advice.Life expectancy < 12 months due to advanced cancer or other life-threatening conditions, such that they will not be able to perform self-care or complete 3 years of follow-up.Pregnant or lactating patients.

Patients will be withdrawn from the study if any of the following criteria apply:
The patient withdraws consentThe patient is no longer able to participate or the investigator, in discussion with the patient’s attending physician(s), decides to terminate participation on medical groundsThe patient becomes pregnant during the study

There will be no participant replacement in the study if a participant withdraws.

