### Randomization

There will be a total of 50 patients recruited, with 25 patients randomized to the intensive arm and 25 patients to the standard care arm. Randomization will be performed by a statistician using computer-generated random number sequence with an allocation ratio of 1:1 for each group.

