## Discussion

Multifactorial interventions of measuring blood glucose, blood pressure and LDL-C have been demonstrated to decrease cardiovascular complications and mortality in type 2 diabetes mellitus [4, 18]. Nurse-managed diabetes mellitus outpatient-management protocols [6], self-monitoring of blood glucose and training in medication adjustment [7] and diabetes self-management education programs are effective in increasing patient knowledge, skills and motivation for disease management with associated improvements in outcomes [19].

With increasing healthcare costs and incidence of diabetes mellitus in Asian countries such as Singapore [2] and the rising availability and use of the Internet, smartphones and social media, facilitating self-monitoring and remote follow-up using technology in patients at high risk of developing diabetic complications is likely to be an increasingly attractive and cost-effective care model compared to frequent hospital visits with healthcare provider-centric treatment. Mobile phones are now omnipresent with worldwide usage rates nearing 100% (96% globally, 128% in developed countries and 89% in developing countries). Singapore has a smartphone user rate of 91% [20, 21]. Technology-enabled diabetes self-management solutions have been shown to significantly improve HbA1c, with the most effective interventions incorporating all the components of a technology-enabled self-management feedback loop that connects people with diabetes mellitus and their healthcare team using two-way communication, analysis of patient-generated health data, tailored education and individualized feedback [8]. On average, mobile phone-based interventions with clinical feedback lead to improvements in HbA1c compared to standard care or other non-mHealth approaches by as much as 0.8% in patients with T2DM, at least in the short term (≤ 12 months) [22].

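### The first-listed secondary endpoint is labelled improved control, yet its ABC limb can be met with no change from week 0

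*Protocol article*

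**What the plan says.** Under Secondary endpoints, the first outcome is the "proportion of patients with documented improved control of risk factors and fulfilment of two or more of the" ABC targets. These are listed as "a) HbA1c < 7%, (b) blood pressure < 140/90 mmHg and (c) LDL-C < 2.6 mmol/L". The sentence continues "and/or two of the following changes in risk factor control" and gives items (d) to (g): minimum falls in HbA1c, systolic pressure, LDL-C and body weight. Only (d) to (g) refer to a change.

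The Methods paragraph of the Abstract describes the same outcome as "proportions of patients with documented improved control of cardiovascular risk factors".

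Eligibility criteria require HbA1c of at least 9%. The other inclusion criteria are age and kidney disease ("Nephropathy as defined by estimated GFR (eGFR) 30–60 ml/min and/or proteinuria"). There is no entry limit on blood pressure or LDL-C. The article expects some patients to be at their blood pressure target, because the renal pharmacist is brought in only "if blood pressure measured during the endocrinologist consultation is not at target and requires more intensive medication titration".

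Randomization gives "25 patients randomized to the intensive arm and 25 patients to the standard care arm".

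**The concern.** The label describes a change, while the ABC limb describes a state. Two of the three states, blood pressure and LDL-C, can already hold at entry. A patient with both at target then satisfies the limb before any intervention, and and/or lets that limb suffice alone.

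Two things are at stake. First, the proportion reported as improved in each arm may include patients in whom nothing improved, and two analysts could classify the same patient differently. Second, patients who succeed by entry status in both arms say nothing about the programme and may dilute the contrast between arms.

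**Working it through.** The article gives no expected rate or power for this endpoint, so there is no figure of its own to reproduce. Its sample size rests on eGFR.

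**1. Which patients can qualify without change.** Take a patient with blood pressure and LDL-C both at target at week 0 and unchanged at the end of follow-up.

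| Item | Week 0 | End | Counts? |
|---|---|---|---|
| HbA1c below 7% | no (entry is at least 9%) | no, even if higher than at entry | no |
| Blood pressure target | yes | yes | yes |
| LDL-C target | yes | yes | yes |
| Two of (d) to (g) | n/a | no | no |

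Two ABC targets are met and the change limb is not. With and/or, the patient is a success.

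**2. Does the word improved exclude this patient?** It does only if improvement is a separate condition. If that condition is two of (d) to (g), the success set becomes (ABC and change) or change. This equals change alone, so the ABC limb would do nothing. If the condition is something else, the article does not define it.

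**3. How many patients (assumed).** The documents give no entry attainment. If 50 to 60% are at each target, independently, the share at both is 0.5 × 0.5 = 0.25 to 0.6 × 0.6 = 0.36. With 40 to 70% at each it is 0.16 to 0.49. Without independence, 50% at each allows anything from 0 to 0.50.

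**4. Dilution if all of them stay at target.** Let q be the share at both targets and p the success rate among the rest. Each arm's rate is q + (1 − q)p, so the difference is (1 − q)(pT − pC). Assume pC = 0.30 and pT = 0.60. Power is exact two-sided Fisher, 25 per arm, alpha 0.05:

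| q | Control | Intensive | Power |
|---|---|---|---|
| 0 | 0.30 | 0.60 | 0.51 |
| 0.10 | 0.37 | 0.64 | 0.42 |
| 0.16 | 0.41 | 0.66 | 0.37 |
| 0.25 | 0.475 | 0.70 | 0.29 |
| 0.30 | 0.51 | 0.72 | 0.25 |
| 0.36 | 0.55 | 0.74 | 0.21 |

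**5. If they do not all stay at target (q = 0.30).**
- 80% stay in both arms: 0.3 × 0.8 + 0.7 × 0.3 = 0.45 v 0.3 × 0.8 + 0.7 × 0.6 = 0.66; power 0.26.
- 70% v 90% stay: 0.21 + 0.21 = 0.42 v 0.27 + 0.42 = 0.69; power 0.42.
- 60% v 90% stay: 0.18 + 0.21 = 0.39 v 0.27 + 0.42 = 0.69; power 0.51, so nothing is lost.

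**6. If they are simply reclassified as failures.** Suppose success requires more targets than at week 0 and these 30% almost never achieve it. The rates are 0.7 × 0.30 = 0.21 v 0.7 × 0.60 = 0.42, with power 0.253. Under the present definition it is 0.254. Certain failures shrink the difference by the same factor (1 − q) as certain successes.

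**7. Adjusting for entry status instead.** I simulated 25 per arm with 30% at both targets at entry, 95% of them staying there, and 30% v 60% among the rest. Power in a linear model was about 0.41 with entry status as a covariate and 0.36 without it.

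**The case against.** The strongest reply is that the sentence asks for improved control and attainment together, so an unchanged patient fails, and that the Abstract also speaks of improvement. This stands as a possible reading, but step 2 shows that it leaves improvement undefined or makes the ABC limb redundant. It shows ambiguity and does not remove the fault.

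A reader might go further and infer that a block of patients is scored as success from the first day whatever the programme does, and that this halves the power. The documents do not support that. They give no share at target. Patients can lose a target over 3 years, and the intensive arm adjusts treatment towards these targets, so better maintenance there could add to the contrast (step 5). The drop from 0.51 to 0.25 also compares the trial with one in which these patients do not exist, and reclassifying them as failures recovers none of it (step 6).

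It is likewise tempting to argue that HbA1c below 7% is out of reach, since it needs a fall of more than 2.0 points from the entry floor, whereas the Discussion cites gains over "non-mHealth approaches by as much as 0.8% in patients with T2DM". That figure is a comparison with other care for mobile-phone programmes over at most 12 months. It does not bound an individual's fall over 3 years, and the point does not need it.

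Finally, the endpoint is secondary. It is listed first but not designated as leading, and the trial is titled a pilot. Randomisation still protects the comparison between arms. The planned logistic regression with potential risk factors leaves room for baseline adjustment. All of this limits the importance of the point. It does not make the label correct.

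**Conclusion.** The point holds as a fault of definition. As written, the endpoint permits a patient already at the blood pressure and LDL-C targets at entry to be reported as improved without change, and the one reading that would prevent this is not defined. This rests on the text alone and needs no assumed figure.

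The effect on power is not established. It depends on the share at both targets at entry and on whether those patients stay at target equally in both arms; neither is in the documents. Under the assumptions shown, with 30% affected, power lies between 0.25 (all stay) and 0.51 (60% v 90% stay), against 0.51 with none affected. If the share is near zero, dilution is negligible. The correction is worth making because it is cheap and stops unchanged patients being reported as improved, not because a given loss of power has been shown.

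**What to change.** In Secondary endpoints, separate target attainment from improvement:

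- **Attainment.** Analyse the number of ABC targets met at 36 months, or attainment of two or more, adjusted for the number met at week 0.
- **Improvement.** Use the label improved only for patients who meet more ABC targets than at week 0 or who meet the change limb (d) to (g).

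This takes one or two sentences and no new data: blood pressure, HbA1c and LDL-C are already collected, and the change limb already needs their baseline values.

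The costs are one more covariate in a 50-patient model, and that patients at both the blood pressure and LDL-C targets at entry can be called improved only through HbA1c or the change limb. For that reason the adjusted attainment analysis should carry the comparison between arms, with the improved proportion reported beside it.
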